Puerto Rico is a US Commonwealth, which provides a unique set of rights and burdens to Puerto Rican individuals. For example, Puerto Rican individuals have US citizenship (41), which may be protective from some, but not all, harms that other Latine groups in the US may experience (42). However, Puerto Ricans individuals living on the island of Puerto Rico do not have voting representation in the US Senate or House of Representatives and are not entitled to electoral votes for presidential elections unless they are living in the continental US (41). Furthermore, policies impacting Puerto Rico place economic burdens on people living on the island (43). For example, the Jones Act, enacted in 1920 and still in effect (with minor gaps throughout the years), mandates that all goods within the coasts of the US (with a few exceptions) must be transported using U.S.-owned and -operated vessels (44). This slows the pace of trade, adds taxes to all shipped goods and disproportionally harms places like Puerto Rico that rely heavily on ocean shipping (43). Thus, the history and political landscape of Puerto Rico likely exert substantial structural influences and SS on Puerto Rican individuals and families and could potentially contribute to higher SUD rates in Puerto Rican adults than in other Latine groups in the US. Examining the role of SS on adolescent substance use risk in a group at higher risk for SUDs is a priority for better understanding the relationship between SS and neurocognitive mechanisms of substance use risk.

In addition to meaningful differences in between Latine subgroups, meaningful differences in SUDs have been found in between Puerto Rican young adults living on the island of Puerto Rico compared to those living on the continental US, such that past-year prevalence of illicit SUD was significantly higher on the continental US (7.8%) than on the island of Puerto Rico (3.7), χ^2^ = 11.1 (45). The two-site design of this pilot study will allow us to explore the relationship between SS and neurocognitive mechanisms of substance use risk in two distinct contexts: the continental US and the island of Puerto Rico. Thus, our preliminary results from our study could indicate if SS are relevant to substance use risk for Puerto Rican children who live on the island of Puerto Rico or on the continental US. The second, larger phase of the study will be better powered to examine site-related differences than the pilot phase.

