**Figure 1 F1:**
[figure not shown]
R61 phase aims. Hypotheses: A substance-use specific composite of structural stressors will relate to brain structure, steeper delay discounting (DD), DD–related brain function, and belief in a just world. DD is theorized to develop alongside belief in a just world, as it is sensible to wait for larger rewards in a just world, where people get what they deserve. Steeper DD may be an adaptive response to an environment high in structural stressors. However, steeper DD is also an established correlate of SUD, and thus, this adaptive response to the environment could increase substance use risk.

**Aim 2, Hypothesis 2, SS & DD:** We expect that greater SS will relate to steeper DD, and less DD-related brain activity in dorsal medial prefrontal cortex, anterior cingulate cortex, insula and ventral striatum. We will use the SS composite variable as a predictor and task-related brain activity in regions of interest (ROIs) as the outcome.

**Aim 3, Hypothesis 3, SS & BJW:** Greater SS composite will relate to weaker BJW.

A moderate effect size association (r > 0.30) found for Hypothesis 1, Hypothesis 2, or Hypothesis 3 will justify progression to the R33 phase.

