**Figure 2 F2:**
[figure not shown]
The ICE formula, from Krieger et al. (22).

Previous studies report a relationship between ICE_income_ and a wide array of health disparities including infant mortality, child mortality, premature mortality, and exposure to black carbon, and it has been effectively used in small geographical units, including at the census tract level (21, 22, 120). ICE_education_ will be calculated within each census tract (i) our participants live in as the number of individuals 25 years or older (Ai) with 4 years of college or more who are White, minus the number of individuals who did not finish high school who are racially minoritized, divided by the total population across all education levels.

Previous analyses of socioeconomic factors in our BYS sample have demonstrated variation in both within and across sites, supporting our ability to examine the research questions described here. For example, within the continental US BYS sample, 56.7% of participants at the young adult assessment reported meeting the federal poverty threshold during young adulthood, while the remaining 43.3% reported not meeting this threshold (108). In the continental US 59.3% of the mothers of our participants had obtained a high school diploma or GED, again demonstrating variation among our sample. In PR, 65.0% of participants met the poverty threshold, and 80.8% of the mothers of our participants had done so in PR (108), demonstrating variation within the PR sample, and across the two sites of the BYS.

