#### Scanning parameters

At both sites, we plan to collect data using a 3T MRI scanner, using a 64-channel coil. For structural scans, a T1-weighted magnetization-prepared rapid acquisition with gradient echo (MPRAGE) sequence will be collected (TR = 1,900 ms, TE = 2.26 ms, FOV = 256 × 256 mm, 176 slices, 1 × 1 × 1 mm^3^ voxel size, flip angle = 9°). For functional, task-based imaging, a gradient-echo T2^*^-weighted EPI sequence (TR = 2,000 ms, TE = 25 ms, 2 × 2 × 2 mm^3^ voxel size, xflip angle = 80°) will be collected.

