#### Assessment of additional covariates

Other covariates of interest also include age, sex, and psychopathology (DISC-IV, for consistency with assessment of the parental generation (125), and the CBCL/6-18) (128). Since ADHD medication are prescribed to more children in the US than any other class of medication (129), and since ADHD medication has been shown to impact neural activity (130), analyses of neural data will take into account ADHD medication, which is reported on the DISC (125).

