### Statistical analyses

We will use generalized linear models (GLMs) using the SS composite variable as a predictor and brain structure in prefrontal regions of interest, DD-performance, neural correlates of DD performance and BJW as outcome variables. These GLMs will also control for family SUD factors, individual experiences of unfair treatment, age, sex, and the presence of a psychiatric diagnosis. Due to the importance of understanding SS alongside other negative exposures, our models will also include adverse childhood experiences, measured using a combination of parent and child report, gathered by interview.

Exploratory analyses will examine the role of each individual SS index on gray matter volume (e.g., the effect of area-level group differences in income alone) and will examine site differences (South Bronx vs. Puerto Rico) in the associations. Site differences may suggest site-specific approaches to prevention and intervention.

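### Site is used only as an exploratory modifier and is not in the main models, so a site mean difference can shift the SS estimate and the r > 0.30 progression decision; a site term costs one degree of freedom

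*Protocol article*

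**What the plan says.** The Statistical analyses section sets out generalized linear models with the SS composite as predictor and prefrontal structure, delay discounting, its neural correlates and belief in a just world (BJW) as outcomes. It lists the adjustment set: "These GLMs will also control for family SUD factors, individual experiences of unfair treatment, age, sex, and the presence of a psychiatric diagnosis". It adds that "our models will also include adverse childhood experiences, measured using a combination of parent and child report, gathered by interview", and the section on additional covariates says that "analyses of neural data will take into account ADHD medication, which is reported on the DISC". None of these names site or scanner.

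Site has a stated role elsewhere. The exploratory analyses "will examine site differences (South Bronx vs. Puerto Rico) in the associations". That asks whether the SS slope differs between sites (an interaction). It does not remove a site mean difference from the main slope.

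The progression rule, under the R61 Specific Aims, reads: "A moderate effect size association (r > 0.30) found for Hypothesis 1, Hypothesis 2, or Hypothesis 3 will justify progression to the R33 phase". It does not say whether r is raw or covariate-adjusted, pooled or within site.

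On the design, the Participants section splits the 72 children equally between the South Bronx and San Juan cohorts. Scanning is done at each site: "At both sites, we plan to collect data using a 3T MRI scanner, using a 64-channel coil". Under Measurement of SS, the violence index comes from the NCVS in the continental US and from the UCR program in Puerto Rico, while the income and education indices both use US census data.

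**The concern.** With two sites of 36, site coincides exactly with place of scanning, with the source of one of the three SS components, and with everything else that separates New York from San Juan. The Background describes the two as distinct contexts. If the composite and an outcome both differ in mean between the sites, for whatever reason, a model without a site term counts the product of those differences as part of the SS association. It adds to a true within-site association if the gaps run in the hypothesised direction and subtracts from it if they run against.

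At stake is the go/no-go decision. It turns on one cut-off, r > 0.30, for any of three hypotheses, and the rule does not fix which r is meant. If that is left open, the choice between a pooled and a site-adjusted r could be made after both are known.

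**Working it through.** **The plan's own figure.** The Power analysis section states that n = 72 detects r = 0.35 with 80% power. Alpha is not stated; I assume 0.05 two-sided. With k covariates, Fisher's z gives

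n = [(1.960 + 0.842) / atanh(0.35)]² + 3 + k, where atanh(0.35) = 0.3654.

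- k = 0: 58.8 + 3 = 61.8, so n = 62. At n = 72 power would be 85.9% and the detectable r 0.325. The stated figure is not reproduced.
- k = 10, about the number of covariates the article names: n = 72, power 80.2%, detectable r 0.349. The stated figure is reproduced. Inflating 62 for about 14% loss (62 / 0.86, or 73) comes close too; the article does not say which was meant.
- k = 11, adding site: power = Φ(0.3654 × √58 − 1.960) = 79.5%, detectable r 0.352.

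**Effect of leaving site out.** Let r_w be the within-site correlation, and d_x and d_y the site gaps in SS and outcome, in within-site SDs. All signs are taken relative to the hypothesised direction. For a 50/50 split:

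pooled r = (r_w + d_x·d_y/4) / √[(1 + d_x²/4)(1 + d_y²/4)]

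P(observed r > 0.30) = 1 − Φ[(atanh 0.30 − atanh r) × √69], with n = 72 and no other covariates.

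The gaps below are assumed, because the documents give none for the composite or any outcome.

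| r_w | d_x | d_y | pooled r | P(r > 0.30) |
|---|---|---|---|---|
| 0.35 | 0 | 0 | 0.35 | 68% |
| 0.35 | 0.5 | −0.5 | 0.27 | 39% |
| 0.35 | 1 | −1 | 0.08 | 3% (2% simulated) |
| 0 | 0 | 0 | 0 | 0.5% |
| 0 | 0.5 | 0.5 | 0.06 | 2% |
| 0 | 1 | 1 | 0.20 | 19% |
| 0 | 1.31 | 1.31 | 0.30 | about 50% |

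For the second row: (0.35 − 0.0625) / 1.0625 = 0.27. For the fifth: 0.0625 / 1.0625 = 0.06.

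**With site in the model.** Removing site means returns r_w whatever the gaps. A simulation of 20,000 trials of 36 + 36 children, at gaps of 1 to 2 SD, confirmed it: P(r > 0.30) stayed at about 0.5% when r_w = 0 and about 69% when r_w = 0.35.

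**Gaps that could be borrowed from the article.** Its site proportions convert to SD units by ln(odds ratio) × √3/π:

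- Maternal high-school completion, 80.8% vs 59.3%: odds ratio 2.89, d = 0.58.
- Illicit SUD, 7.8% vs 3.7%: odds ratio 2.20, d = 0.44.
- Poverty, 65.0% vs 56.7%: odds ratio 1.42, d = 0.19.

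With 0.58 and 0.44 as illustrative gaps, the spurious r is (0.58 × 0.44 / 4) / √(1.084 × 1.048) = 0.06. Run in opposite directions against a true 0.35, they give (0.35 − 0.064) / 1.066 = 0.27. These proportions do not measure the study's exposure or outcomes, so they only suggest an order of magnitude.

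**The case against.** **The article's figures do not show confounding.** A reader might infer from "In PR, 65.0% of participants met the poverty threshold, and 80.8% of the mothers of our participants had done so in PR" and "past-year prevalence of illicit SUD was significantly higher on the continental US (7.8%) than on the island of Puerto Rico (3.7" that site is already shown to be related to both exposure and outcome, and that the income and education components point in opposite directions. The documents do not support that. The poverty and schooling figures describe individuals and families in the earlier BYS generation; the exposure is a tract-level contrast between groups. Illicit SUD in young adults is not an outcome here, and parental young-adult SUD is already a covariate. This stands in full.

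**Scanner and data source are only partial arguments.** Field strength, coil and sequence are the same at both sites, so a scanner offset is an inference, and it could not affect BJW or discounting behaviour. Only the violence component has different sources. This stands too, but it leaves differences of context, which need no scanner effect.

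**Between-site contrast may be wanted.** The Background treats the island's political and economic position as a source of SS, and Measurement of SS counts variation across sites as useful. A site term removes that contrast from the main estimate. This is a real cost, and the reason to report the pooled estimate as well.

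**The article is condensed.** Its covariate list is spread over sections (ADHD medication is named elsewhere), and a fuller protocol may say more. That would be a good answer if site were simply unmentioned. But the text gives site a specific role, exploratory and as a modifier, while naming the main adjustment set. The remark that the next phase will be better powered for site differences concerns comparing sites, not adjusting for them.

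**Conclusion.** The point holds as a cheap improvement that should be made, not as a flaw that invalidates the pilot. As written, the main models and the r > 0.30 rule are not protected against a site mean difference, and two equal sites make site inseparable from context, place of scanning and the violence data source.

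The size depends wholly on gaps that the documents do not give. Loss of a true signal is the nearer risk: opposite gaps of 0.5 SD each lower a within-site r of 0.35 to about 0.27, and the chance of passing the rule from about 68% to 39%. A reader might go further and conclude that site differences alone could readily produce a passing result or reverse a true one. That is not supported: same-direction gaps of 0.5 SD create only about 0.06, and an expected 0.30 from nothing needs about 1.3 SD in both variables. Nothing in the documents indicates gaps that large.

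The calculations assume an even 36/36 split, equal slopes and spreads within sites, and no absorption of the site gap by the listed covariates. Those may take up part of it but cannot stand in for site.

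**What to change.** In the Statistical analyses section, add site (South Bronx or Puerto Rico) as a fixed effect in every main model. In the R61 Specific Aims, define the progression r as the site-adjusted partial correlation between the SS composite and the outcome. Report the estimate without the site term beside it, so that any between-site contribution is visible. Keep the SS-by-site interaction exploratory. Leave the composite and its components on one common scale: standardising them within each site is not needed and would rescale a shared index differently by site.

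The cost is a sentence in each place and one degree of freedom: power at r = 0.35 goes from about 80.2% to 79.5%, and the detectable r from 0.349 to 0.352, on the assumption of about ten other covariates. No new data are needed. Any genuine between-site SS contrast leaves the main estimate but remains in the pooled one. The choice should be fixed before outcome data are seen.

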## Discussion

While SS, measured as area-level differences among groups, is recognized as a fundamental cause of disparities in health, it is currently unclear what are important mechanisms through which SS contributes to substance use risk in youth at high risk for substance use disorders. Characterizing how higher levels of SS could lead to greater risk via neurocognitive processes and elucidating specific brain-based mechanisms can improve understanding of neural correlates of SS and may provide compelling evidence to lawmakers to enact on structural change. The goal of an investigation with these objectives is to inform structural and family-level interventions aimed at reducing health disparities. While structural interventions are likely the best solution to eliminate structural disparities, elucidating mechanisms that can be modified can provide families with actionable information could allow families to make their own decisions and improve the wellbeing of their children. This is particularly important in situations and times periods when it is difficult to make structural changes to reduce health disparities.

Establishing the harms associated with SS and relevant mechanisms is necessary and important. However, also important is improving understanding of family-level protective and promotive factors. Thus, in the next phase of this study, we plan to examine factors that may prevent substance use in adolescence, as well as promotive factors. In addition, we plan to examine the moderating effect of family-level protective factors and explore how cultural factors can influence risk for SUD (134, 135) to determine if they can buffer the negative impact of SS on neurocognitive mechanisms of substance use risk. The long-term goal of this future work is to identify culturally relevant protective factors at the area-, family- and individual-level that can meaningfully inform lines of prevention and intervention.

Improved understanding of the relationship between SS indicators and mechanisms of substance use risk could shape future research examining the relationship between SS and substance use, as well as novel prevention and intervention efforts at the structural level, the desirable approach to addressing structural disparities and fundamental causes. Furthermore, results at the individual-level could suggest interventions such as episodic future thinking, which is aimed at helping individuals prioritize larger, later rewards over smaller, sooner rewards, could target reward-related decision making, as this intervention reduced DD and risky behaviors (136). Thus, the current study aims to examine the relationship between SS and mechanisms of substance use risk, in the service of informing future efforts at reducing the risk of adolescent substance use.
